### Withdrawal of participants

Study drug must be discontinued if:
The participant develops elevated serum ALT/AST four times above the upper limit of normal;The participant decides she/he no longer wishes to continue;Cessation of study drug is recommended by the investigator.

Should a patient withdraw from study drug only, efforts will be made to continue to obtain follow-up data, with the permission of the patient.

Participants who wish to withdraw from study medication will be asked to confirm whether they are still willing to provide the following:
Study specific data at follow-up visits 5–19;End of study data as per visit 19, at the point of withdrawal;Questionnaire data collected as per routine clinical practice at annual follow-up visits.

If participants agree to any of the above, they will be asked to complete a confirmation of withdrawal form to document their decision.

### Data monitoring, quality control and quality assurance

#### Data collection

To preserve confidentiality, all patients will be allocated a unique study identification number, which will be used on all data collection forms and questionnaires. Only a limited number of members of the research team will be able to link this identification number to identifiable details, which will be held on a password-protected database. All study documentation will be held in secure offices and the research team will operate to a signed code of confidentiality. A clinical data management software package will be used for data entry and processing, allowing a full-audit trail of any alterations made to the data post entry. Original questionnaires, case report forms and consent forms will be securely archived at the Newcastle upon Tyne Hospitals NHS Foundation Trust archive facility for 15 years following publication of the last paper or report from the study. Data will be handled, computerised and stored in accordance with the Data Protection Act 1998. No participant identifiable data will leave the study site. The quality and retention of study data will be the responsibility of the chief investigator. All study data will be retained in accordance with the latest Directive on GCP (2005/28/EC) and local policy. All laboratory samples will be stored and identified using the patient's unique study identification code.

#### Discontinuation rules

The study may be prematurely discontinued on the basis of new safety information, or for other reasons given by the DMEC and/or Trial Steering Committee (TSC), Sponsor, regulatory authority or Research Ethics Committee concerned.

#### Monitoring, quality control and quality assurance

The study will be managed through the NCTU. The Trial Management Group (TMG) will include the chief investigator, senior trial manager, trial manager, assistant trial manager, data manager and other members of the trial team when applicable. NCTU will provide day-to-day support for the site and provide training through investigator meetings, site initiation visit and routine monitoring visits. Protocol amendments will be managed by the NCTU and communicated to the trial team.

#### Data Monitoring and Ethics Committee

An independent DMEC has been appointed. It will consist of two physicians not connected to the study and one independent statistician and will be convened to undertake independent review. The purpose of this committee will be to monitor efficacy and safety end points. Only the DMEC will have access to unblinded study data. The committee will meet a minimum of three times, at the start, middle and completion of the study.

#### Trial Steering Committee

A TSC will be established to provide overall supervision of the study. The TSC will consist of an independent chair, two independent clinicians, independent consumer representative, the chief investigator, co-investigator, senior trial manager, trial manager and trial statistician. Representatives of the trial sponsor and funder should be invited to all TSC meetings. The committee will meet every 3 months during recruitment, and annually thereafter for the duration of the study.

#### Study monitoring

Monitoring of study conduct and data collected will be performed by a combination of central review and site monitoring visits to ensure the study is conducted in accordance with good clinical practice (GCP). Study site monitoring will be undertaken by the trial manager. The main areas of focus will include consent, serious adverse events (SAEs), essential documents in study site files and drug accountability and management. All monitoring findings will be reported and followed up with the appropriate persons in a timely manner. The study may be subject to inspection and audit by the Newcastle upon Tyne Hospitals NHS Foundation Trust under their remit as sponsor, and other regulatory bodies to ensure adherence to GCP.

### Recording and reporting serious adverse events or reactions

All adverse events (AEs) should be reported. Depending on the nature of the event, the reporting procedures below should be followed. Any questions concerning AE reporting should be directed to the chief investigator or the named contact within the management team within the NCTU in the first instance.

#### Adverse event (including adverse reaction)

All non-SAEs/reactions during drug treatment will be reported on the study case report form (CRF) and sent to the NCTU management team within 2 weeks. Severity of AEs will be graded on a five-point scale (Mild, Moderate, Severe, Life threatening, causing death). Relation of the AE to the treatment should be assessed by the investigator at site. The individual investigator at each site will be responsible for managing all AEs/reactions according to local protocols.

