**Methods and analysis:**

RITPBC is a Medical Research Council (MRC) and National Institute for Health Research (NIHR) Efficacy and Mechanism Evaluation Programme (EME)-funded project. It is a phase II, single-centre, randomised controlled, double-blinded trial comparing rituximab with placebo in fatigued PBC patients. 78 patients with PBC and moderate to severe fatigue will be randomised to receive two infusions of rituximab or placebo. The study aims to assess whether rituximab improves fatigue in patients with PBC, the safety, and tolerability of rituximab in PBC and the sustainability of any beneficial actions. The primary outcome will be an improvement in fatigue domain score of the PBC-40, a disease-specific quality of life measure, evaluated at 12-week assessment. Secondary outcome measures include novel MRS techniques assessing muscle bioenergetic function, physical activity, anaerobic threshold and symptom, and quality of life measures. The trial started recruiting in October 2012 and recruitment is ongoing.

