## Methods/design

### Study design

RITPBC is a phase II, single-centre, randomised controlled, double-blinded trial comparing rituximab with placebo in fatigued PBC patients. A total of 78 patients (39/arm) with definite or probable PBC and moderate–severe fatigue (PBC-40 fatigue domain score >33) will be recruited. The primary outcome is improvement in fatigue severity, assessed using the PBC-40, a disease-specific quality of life measure,^12^ which will be evaluated at baseline and at 12 weeks. The secondary objectives will be to explore the extent to which any such improvement in fatigue is related to a reduction in the level of anti-PDH antibody and to any associated effect on biomarkers of bioenergetic function assessed using novel MRS protocols. Other secondary outcome measures are improvement in AT, physical activity levels, liver biochemistry, daytime somnolence, autonomic symptoms, functional status, cognitive dysfunction and anxiety and depressive symptoms. The safety of rituximab in PBC will be explored and the sustainability of any beneficial actions evaluated.

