### Eligibility criteria

**Inclusion criteria**Age ≥18 yearsPatient has capacity and provided written informed consent for participation in the study prior to any study-specific proceduresModerate or severe fatigue as assessed using previously designated cut-offs of the PBC-40 fatigue domain score (ie, fatigue domain score >33)Presence of AMA at a titre of >1:40Adequate haematological function haemoglobin >9 g/L, neutrophil count >1.5×10^9^/L, platelet count >50×10^9^/LBilirubin <50 µmolInternational normalised ration ≤1.5Child-Pugh score <7Eastern Cooperative Oncology Group (ECOG) performance status <2Adequate renal function; Cockcroft and Gault estimation >40 mL/minWomen with child-bearing potential should have a negative pregnancy test prior to study entry and be using an adequate contraceptive method which must be continued for 12 months after completion of treatment**Exclusion criteria**History or presence of other concomitant liver diseases (including hepatitis due to hepatitis B or C or evidence of chronic viraemia on baseline screening), primary sclerosing cholangitis or biopsy-proven non-alcoholic steatohepatitisAverage alcohol ingestion >21 units/week (male) or >14 units/week (female)Chronic sepsis or intercurrent condition likely to predispose to chronic sepsis during the studyPrevious history of aberrant response or intolerance to immunological agentsPresence of significant untreated intercurrent medical condition itself associated with fatiguePresence of significant risk of depressive illness (Hospital and Anxiety and Depression Scale (HADS) score indicating caseness)Current statin therapy or statin therapy within 3 months of enrolmentOngoing participation in other clinical trials or exposure to any investigational agent 4 weeks prior to baseline or within <5 half-lives of the investigational drugMajor surgery within 4 weeks of study entryVaccination within 4 weeks of study entry; patients requiring seasonal flu or travel vaccines will be required to wait a minimum of 4 weeks postvaccination to enrol in the studyPregnant or lactating womenPsychiatric or other disorder likely to impact on informed consentThe patient is unable and/or unwilling to comply with treatment and study instructionsAny other medical condition that, in the opinion of the investigator, would interfere with safe completion of the studyHypersensitivity to the active substance (rituximab) or to any of the excipients (sodium citrate, polysorbate 80, sodium chloride, sodium hydroxide, hydrochloric acid, water (for injection)) or to murine proteinsActive, severe infections (eg, tuberculosis, sepsis or opportunistic infections)Known HIV infectionClinical history of latent tuberculosis infection unless the patient has completed adequate antibiotic prophylaxisAlanine transaminase (ALT)/aspartate transaminase (AST) 4× upper limit of normalSevere immunocompromised stateSevere heart failure (New York Heart Association (NYHA) Class IV) or severe uncontrolled cardiac diseaseMalignancy (other than basal cell carcinoma) within the last 10 yearsDemyelinating diseasePrevious participation in this studyAny contraindication to rituximab therapy not covered by other exclusions

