
### Intervention

Patients in the study will be randomised on a 1:1 ratio to receive either:
Rituximab 1 g on days 1 and 15—study drug250 mL 0.9% sodium chloride on days 1 and 15—placebo.

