#### Primary outcome

Differences between intervention and control groups at 12 weeks on PBC-40 fatigue domain scores will be analysed by analysis of covariance (ANCOVA) using baseline scores as covariates. The time course of the comparison between intervention and control groups over the 12-month follow-up period will be assessed using repeated measures analysis of variance.

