#### SAE/SAR (including SUSARs)

All SAEs, SARs and SUSARs during drug treatment shall be reported to the chief investigator within 24 h of the site learning of its occurrence. The initial report can be made by secure fax which will also generate an email copy to the chief investigator, senior trial manager and trial manager. In the case of incomplete information at the time of initial reporting, all appropriate information should be provided as follow-up, on the appropriate SAE follow-up form. As indicated above, relationship of the SAE to the treatment (causality) should be assessed by the investigator at the site, as should the expected or unexpected nature (by reference to the SmPC for rituximab) of any serious adverse reactions (SARs). The MHRA and main REC will be notified by the chief investigator or trials management team (on behalf of the Sponsor) of all SUSARs occurring during the study according to the following timelines: fatal and life-threatening within 7 days of notification and non-life-threatening within 15 days. All investigators will be informed of all SUSARs occurring throughout the study on a case-by-case basis. The chief investigator will ensure the Newcastle upon Tyne Hospitals NHS Foundation Trust as Sponsor is notified of any SUSARs in accordance with local trust policy.

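### The safety sections contradict each other on the reporting period; read literally, the operative rules leave about 96% of the 12-month follow-up outside routine AE and SAE reporting

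*Protocol article*

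**What the plan says.** The section on recording and reporting serious adverse events or reactions begins with a general instruction: "All adverse events (AEs) should be reported". It then refers the reader to procedures set out below it, which differ by the nature of the event.

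Two subsections give those procedures.
- Non-serious events: "All non-SAEs/reactions during drug treatment will be reported on the study case report form (CRF".
- Serious events: "All SAEs, SARs and SUSARs during drug treatment shall be reported to the chief investigator within 24 h".

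The serious-event subsection goes on to describe onward notification of SUSARs to the regulator, the ethics committee and the investigators. Those sentences refer to the study as a whole, not to the treatment period.

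The Abstract says that participants are "randomised to receive two infusions of rituximab or placebo", and the Intervention section gives the days: "Rituximab 1 g on days 1 and 15", with placebo on the same days. The Primary outcome analysis extends well beyond dosing: "The time course of the comparison between intervention and control groups over the 12-month follow-up period" is to be assessed.

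Safety is an explicit objective in Study design: "The safety of rituximab in PBC will be explored and the sustainability of any beneficial actions evaluated". The Secondary outcome section lists safety and tolerability among the outcomes to be reported. The DMEC is to monitor safety end points and to meet at the start, middle and completion of the study.

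**The concern.** The two rules that tell staff what to record, and whom to tell, both stop with drug treatment. The general instruction above them and the SUSAR sentences below them do not stop there. Staff who follow the procedures to the letter would stop recording soon after the second infusion; staff who follow the opening sentence would record to the end.

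This matters because the article plans to look for benefit over 12 months and to judge safety in the same trial. If harms were collected over a much shorter period than benefits, the safety outcome would under-count post-infusion events in both arms. The DMEC would see only what had been reported to it. A conclusion that the drug was well tolerated could then partly reflect the collection period.

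**Working it through.** The article states no figure for the safety reporting window, so there is none to reproduce. The check has two parts: what the limiting phrase can mean, and how much follow-up each meaning leaves out.

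**1. What the phrase can mean**

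The article does not define the treatment period. Its usage elsewhere mostly separates treatment from follow-up:
- Eligibility criteria: contraception "must be continued for 12 months after completion of treatment". This is cited only to show that treatment is regarded as ending; it says nothing about the period for adverse events.
- B-cell biology: the primary end point is placed 12 weeks after therapy, with a secondary follow-up period to 12 months.
- Withdrawal of participants: visits 5 to 19 are called follow-up visits.
- Concomitant medications: where the whole study is meant, the text says so.

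One place is looser. The Sample size calculation describes the primary outcome as measured after 12 weeks of intervention, which would allow a reading to week 12.

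**2. Share of follow-up outside the window**

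Inputs: last infusion on day 15 (Intervention); follow-up of 12 months (Primary outcome), taken as 365 days.

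Formula: share outside = 1 − (last day of window ÷ 365).

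| Reading | Last day | Inside | Outside |
|---|---|---|---|
| Literal, days 1 to 15 | 15 | 15/365 = 4.1% | 95.9% |
| Assumed 28 days post-dose | 15 + 28 = 43 | 43/365 = 11.8% | 88.2% |
| Assumed 30 days post-dose | 15 + 30 = 45 | 45/365 = 12.3% | 87.7% |
| To week 12 from first infusion | 84 | 84/365 = 23.0% | 77.0% |
| To week 12 from second infusion | 15 + 84 = 99 | 99/365 = 27.1% | 72.9% |
| Whole study | 365 | 100% | 0% |

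The literal figure hardly depends on conventions. With the last day at 14 to 16 and follow-up at 364 to 380 days, the share outside runs from 95.6% to 96.3%.

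**3. Which events lose their route**

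Under a restricted reading, for events after the window closes:
- Non-serious events: the only CRF rule is limited to drug treatment, so no procedure applies.
- SAEs that are not SUSARs: the only rule for reporting to the chief investigator has the same limit.
- SUSARs: onward notification is study-long, but it starts from an SAE that has been reported and then assessed for causality and expectedness. If the SAE is not reported, the SUSAR may not be recognised.

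The study-long SUSAR sentences therefore depend on a first step that the same subsection limits in time.

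**The case against.** The strongest reply is that the section does not confine reporting to the treatment period. Its first sentence has no time limit, and it says that the procedures vary with the nature of the event, not its timing. The SUSAR sentences presuppose that serious events are captured throughout. The DMEC reviews safety to completion, site monitoring names SAEs as a focus, and the study can be stopped on new safety information. All of this points to an intention beyond day 15. The limiting phrase is undefined, the schedule of events is in a figure that is not shown, and the article condenses a full protocol that may set the period.

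Much of this stands. A reader might infer that reporting is definitely confined to days 1 to 15. The documents do not support that: it is the literal reading of an undefined phrase, and other sentences in the section contradict it. A reader might also infer that the safety aim cannot be answered. That does not follow either: infusion-period tolerability is captured on any reading, and the opening sentence, if followed, captures the rest.

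What the reply does not remove is the contradiction. The article states a window twice, in its two operative rules, so this is not merely detail left to a fuller document. The opening sentence defers to those rules, and DMEC review and site monitoring do not set a collection period. A full protocol with a clear period would settle practice, but the article's wording would still need correcting.

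**Conclusion.** The point holds as an internal contradiction with a practical consequence. The general instruction and the SUSAR sentences imply study-long reporting; the operative rules for non-serious and serious events are limited to drug treatment. On the literal reading, about 96% of follow-up is outside routine reporting. On the more generous restricted readings the share is about 88% (an assumed 28 to 30 day post-dose window) or about 77% (week 12 counted from first infusion). On the study-long reading it is nil.

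These figures are shares of follow-up time, not of events. The article gives no adverse event rates and no timing of events, so the number that might be missed cannot be estimated from it. If events cluster around the infusions, the share missed would be smaller than the share of time. The conclusion is that the safety outcome and the DMEC's review could under-count post-infusion events, not that they will.

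**What to change.** Reconcile the opening paragraph and the two subsections. In both subsections, replace the limit to drug treatment with one stated observation window, the same for both arms, running from the first infusion to the final 12-month visit. This agrees with the unrestricted opening sentence and the study-long SUSAR wording. Record non-serious events at visits already scheduled. Keep the existing 24 h rule for serious events, which should not wait for a visit. Report safety by arm over that window.

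Forty participants had already been infused when the article was written, so the report should also state which period was applied to them in practice.

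The cost is an amendment to the protocol wording and the CRF, and modestly more adverse event recording. No extra visits are needed.

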#### SAE/SAR (including SUSARs)

All SAEs, SARs and SUSARs during drug treatment shall be reported to the chief investigator within 24 h of the site learning of its occurrence. The initial report can be made by secure fax which will also generate an email copy to the chief investigator, senior trial manager and trial manager. In the case of incomplete information at the time of initial reporting, all appropriate information should be provided as follow-up, on the appropriate SAE follow-up form. As indicated above, relationship of the SAE to the treatment (causality) should be assessed by the investigator at the site, as should the expected or unexpected nature (by reference to the SmPC for rituximab) of any serious adverse reactions (SARs). The MHRA and main REC will be notified by the chief investigator or trials management team (on behalf of the Sponsor) of all SUSARs occurring during the study according to the following timelines: fatal and life-threatening within 7 days of notification and non-life-threatening within 15 days. All investigators will be informed of all SUSARs occurring throughout the study on a case-by-case basis. The chief investigator will ensure the Newcastle upon Tyne Hospitals NHS Foundation Trust as Sponsor is notified of any SUSARs in accordance with local trust policy.

#### Insurance and finance

The Newcastle upon Tyne Hospitals NHS Foundation Trust has liability for clinical negligence that harms individuals towards whom they have a duty of care. National Health Service (NHS) Indemnity covers NHS staff and medical academic staff with honorary contracts conducting the study for potential liability in respect of negligent harm arising from the conduct of the study. The Newcastle upon Tyne Hospitals Foundation NHS Trust is sponsor and through the sponsor, NHS indemnity is provided in respect of potential liability and negligent harm arising from study management. Indemnity in respect of potential liability arising from negligent harm related to study design is provided by NHS schemes for those protocol authors who have substantive contracts of employment with the NHS and by Newcastle University Insurance schemes for those protocol authors who have substantive contract of employment with Newcastle University. This is a non-commercial study and there are no arrangements for non-negligent compensation.

## Dissemination

The data will be the property of the chief investigator and co-investigator(s). Publication will be the responsibility of the chief investigator. It is planned to publish this study in peer-review journals and to present data at national and international meetings. Results of the study will also be reported to the sponsor and funder, and will be available on their web site. All manuscripts, abstracts or other modes of presentation will be reviewed by the TSC and funder prior to submission. Individuals will not be identified from any study report. Participants will be informed about their treatment and their contribution to the study at the end of the study, including a lay summary of the results.

